## Abstract

**Background:**

Children with an intellectual disability are at increased risk of psychosocial problems. This leads to serious restrictions in the daily functioning of the children and to parental stress. Stepping Stones Triple P aims to prevent severe behavioural, emotional and developmental problems in children with a (intellectual) disability by enhancing parenting knowledge and skills, and the self-confidence of parents. This paper aims to describe the design of a study of the effectiveness of parenting counselling using Stepping Stones Triple P compared to Care as Usual.

**Methods/Design:**

The effects of Stepping Stones Triple P will be studied in a Randomised Controlled Trial. Parents of children aged 5-12 years with an IQ of 50-85 will be recruited from schools. Prior to randomisation, parents complete a screening questionnaire about their child's psychosocial problems and their parenting skills. Subsequently, parents of children with increased levels of psychosocial problems (score on Strengths and Difficulties Questionnaire ≥ 14) will be invited to participate in the intervention study. After obtaining consent, parents will be randomised either to the experimental group (Stepping Stones Triple P) or to Care as Usual. The primary outcome is a change in the child's psychosocial problems according to parents and teachers. The secondary outcome is a change in parenting skills. Data will be collected before the start of the intervention, immediately after the intervention, and six months after.

**Discussion:**

This paper presents an outline of the background and design of a randomised controlled trial to investigate the effectiveness of Stepping Stones Triple P, which aims to decrease psychosocial problems in children with a mild intellectual disability. Stepping Stones Triple P seems promising, but evidence on its effectiveness for this population is still lacking. This study provides evidence about the effects of this intervention in a community-based population of children with a mild intellectual disability.

## Background

Psychosocial problems, such as problems with behaviour, emotions and relationships, occur frequently in children with an intellectual disability (ID). Estimates of their prevalence rates vary widely, from 30% to over 60% [1-3]. The combination of psychosocial problems and ID significantly limits occupational opportunities in the post-school period and can also lead to major restrictions in participation in educational and recreational programmes [4]. Moreover, a child's psychosocial problems and parenting stress exacerbate each other over time [5]. Further, the presence of psychosocial problems also leads to parental stress due to parenting challenges [6,7].

The improvement of parenting skills by parenting interventions may lead to a significant reduction in both the psychosocial problems of the child and the parental stress [8]. A promising parenting programme that may help to reduce these problems in these children is Stepping Stones Triple P (SSTP). SSTP aims to prevent severe behavioural, emotional and developmental problems in children with a disability by enhancing the knowledge, skills and confidence of parents [9]. However, although SSTP looks promising, there is little strong evidence on its effectiveness. There are two studies in Australia in preschool-aged children with developmental disabilities and problem behaviour [10,11]. Furthermore, there is a study in Australia on children diagnosed with autism spectrum disorders [12]. The results of these studies demonstrate maintained significant improvements in child behaviour and parenting styles, and parents reported a high level of satisfaction with SSTP. A recent Dutch study on SSTP without control groups shows positive effects on the child's psychosocial problems, on parenting skills, family functioning and parental wellbeing [13]. However, there is no evidence with Randomised Controlled Trials (RCT) for SSTP among this broad target population of children with mild ID and their parents.

The aim of this study is to assess the effectiveness of SSTP regarding the reduction of a child's psychosocial problems and parental stress among children with mild ID and their parents. This paper describes the design of the evaluation of the effectiveness of parenting counselling according to SSTP regarding the psychosocial problems of children with mild ID compared to a control group receiving Care as Usual (CAU).

## Methods/Design

### Trial design

The design of the study will be described following the CONSORT guidelines [14]. The study will be conducted as an RCT on the effectiveness of parenting counselling according to SSTP compared to a control group receiving CAU (Figure 1). There will be a screening before the intervention (T0), an assessment immediately after the intervention (T1) and a follow-up assessment after six months (T2). Parents will participate voluntarily in this study and are free to leave the study at any time. All parents will provide written informed consent before they participate in the study. Ethical permission for this study has been obtained from the Medical Ethics Committee of the University Medical Center Groningen. The study will be performed between October 2010 and December 2013.

**Figure 1 F1:**
[figure not shown]
**Study design**. This figure describes the design of an RCT on the effectiveness of parenting counselling according to SSTP compared to a control group receiving CAU.

### Participants

Via schools, parents of children aged 5-12 years with an IQ of 50-85, living in the four Northern provinces of the Netherlands (Groningen, Friesland, Drenthe and a part of Overijssel) will be invited to fill out a screening questionnaire about their child's psychosocial problems and their parenting skills. The majority of children with mild ID attend three types of school for special educational needs in the Netherlands, in Dutch called 'SBO', 'REC3' and 'REC4'. SBO ('Speciaal Basis Onderwijs'; special primary education) comprises children with mild intellectual disabilities (IQ of between 70 and 85), learning difficulties and/or behaviour difficulties. REC 3 ('Regional Expertise Center cluster 3') includes children with physical disabilities, (mild) ID (IQ < 55 or IQ between 56 and 70 with other severe disabilities), and/or chronic diseases. REC 4 ('REC cluster 4') includes children with psychiatric and/or behavioural disorders with or without mild ID (IQ > 70) [15,16]. Participating schools expect that 30% of the REC4 pupils, 30% of the REC3 pupils and 95% of the SBO pupils will be eligible for screening (age 5-12 years and IQ 50-85).

In order to increase response rates, we will offer assistance if required to fill out the screening questionnaire and will visit all families to fill out the second and third questionnaires [1]. Exclusion criteria are: (1) the child lives in residential care (except foster care), (2) parents are unable to speak Dutch, (3) information about the child's IQ is not available, and (4) parents live outside the research area.

When parents report psychosocial problems in their child at T0, they will be invited to participate in the intervention study. Exclusion criteria are: (1) a brother or sister (with a higher Strengths and Difficulties Questionnaire (SDQ) score) is participating in the study, and (2) the parents are receiving treatment for parenting skills or other treatment that potentially clashes with SSTP.

### Intervention

SSTP is a family intervention and aims to prevent severe behavioural, emotional and developmental problems in children with all kinds of disabilities, including mild ID, by enhancing the knowledge, skills and confidence of parents [9]. This method is part of the Australian Triple P - Positive Parenting Program, a system of parenting and family interventions for parents of children who have or are at risk of psychosocial problems [17]. There are seven principles of parenting in SSTP: (1) ensure a safe interesting environment, (2) create a positive learning environment, (3) use assertive discipline, (4) have realistic expectations, (5) take care of oneself as a parent, (6) family adaptation to having a child with a disability, and (7) be part of the community. The last two principles are additional ones, specifically related to the parenting of children with a disability [10].

SSTP takes 8-10 individual sessions, provided over 10-12 weeks. Each session typically lasts 60-120 minutes. The first module, 'Assessment', consists of two sessions of about 60-90 minutes. In this module, parents formulate hypotheses about the problems and make relevant causes and factors clear. The second module, 'Positive Parenting', also consists of two sessions of about 60-90 minutes. In these sessions parenting strategies should be introduced to parents. The third module, 'Practice', consists of three sessions of about 40-60 minutes. In these sessions, parents will practise the parenting strategies and receive support. The final module, 'Planned Activities Training', consists of three sessions. Parents will be assisted in the practical implementation of the strategies [9].

### Control condition

Participants assigned to the control condition may utilise any service, except SSTP. These services can be anything aimed to alleviate parental stress or the psychosocial problems of the child. CAU can consist of Practical Pedagogical Family Support (PPG), Video-home training (VHT), Intensive Pedagogical Homecare (IPT) or Intensive Orthopedagogical Family Care (IOG), but also of psychiatric or psychological care for the child and, in some cases, no care at all [18].

### Outcome measures

The primary outcome is the child's psychosocial problems measured by the SDQ (parent and teacher versions) and the Eyberg Child Behaviour Inventory (ECBI). The SDQ is a 25-item questionnaire, covering emotional symptoms, conduct problems, hyperactivity, peer relationship problems, pro-social behaviour and the impact of the problems on functioning [19]. We will use two informants to measure each child's psychosocial problems (i.e. the teacher and the parent). Multiple informants on a child's psychosocial problems are invaluable for understanding the home and community functioning of children with mild ID, because psychosocial problems may be highly situational and differ at school and at home [20-22]. The ECBI, a 36-item questionnaire, will be used to measure parental perceptions of the disruptive behaviour of the child, including frequency and its identification as a problem [23].

The secondary outcome is parenting skills measured by the Parenting Stress Index (PSI) and the Alabama Parenting Questionnaire (APQ). The PSI measures parents' perceived stress due to parenting. The short 25-item version of the PSI comprises questions on experience of parenting leading to a total 'parenting stress' score [24]. The APQ measures parenting practices. The short version of the APQ consists of 35 items categorised into four subscales: parental involvement, positive parenting, poor monitoring and inconsistent discipline [25].

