### Sample size

The parental SDQ score will serve as the primary outcome measure to determine the sample size. For a 3-point decrease in the SDQ total score, given a standard deviation (SD) of the SDQ of 6 points (an effect size of 0.5), at alpha = 0.05 (two-sided) and beta = 0.20, 63 children need to be included in each group (SSTP and CAU). With adjustment for a 'loss to follow-up' of about 40%, 210 children need to be included in the study, 105 children in each treatment condition.

Parents will be included if their child has an SDQ total problems score of 14 or higher. The prevalence rate of an SDQ ≥ 14 among children who are not under current treatment for their mental health problems is estimated at 55% [2]. Therefore, (2 × 105)/55% = 381 children with mild ID aged 5-12 years are required. Adjusting for 30% refusal to participate and 10% incomplete SDQs, 635 parents will have to fill in the SDQ.

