### Statistical analyses

The results will be analysed on an intention to treat principle with all randomised participants, using all follow-up measures. Consequently, participants who filled out the questionnaire will be included in the analyses, regardless of whether or not they have completed the intervention.

The baseline characteristics of the parents in both research groups will be compared using Chi-squared tests for nominal and ordinal variables, and t-tests for continuous variables. The differences between the intervention and control condition over time will be assessed by mixed model techniques to consider factors that may influence the outcomes. If necessary, data on subjects lost to follow-up will be handled by extrapolation of the last observation or by sophisticated imputation techniques. Changes in the child's psychosocial problems and parenting characteristics will be expressed as standardised effect sizes with 95% confidence intervals. The CONSORT guidelines will be followed [14]. All the analyses will be carried out using SPSS 17.0.

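### Three measures are jointly primary, but alpha and power are set for only one of them, the parent SDQ

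*Protocol article*

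**What the plan says.** The Outcome measures section of the protocol article reads: "The primary outcome is the child's psychosocial problems measured by the SDQ (parent and teacher versions) and the Eyberg Child Behaviour Inventory (ECBI"). This gives two instruments and three measures: parent SDQ, teacher SDQ and ECBI. The ECBI is a parent report and is described as "including frequency and its identification as a problem", so it may yield two scores. The section does not order the measures.

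Abstract, Methods/Design: "The primary outcome is a change in the child's psychosocial problems according to parents and teachers".

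Sample size: "The parental SDQ score will serve as the primary outcome measure to determine the sample size". The planning difference is 3 points with an SD of 6, an effect size of 0.5. Two-sided alpha is 0.05 and power is 80%, which leads to 63 evaluable children per arm. Allowing for 40% loss brings this to 105 randomised per arm, 210 in total.

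Trial design sets two assessments after the intervention: T1 directly afterwards and T2 at six months. Statistical analyses plans mixed models of the group difference over time, "using all follow-up measures".

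**The concern.** The sample size section gives one error rate and one power, both for a single test of one measure. The outcome section gives primary status to three measures. The two fit together only if the other two measures play no part in the primary claim, and the outcome section says that they do.

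The meaning of the stated 5% and 80% then depends on how the three results are combined. If one positive measure is enough, the false-positive rate exceeds 5%. If all must be positive, the error rate is held but power is below 80%.

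A split result is foreseeable. The article itself argues that a child's problems can differ between home and school, which is why it uses two informants. Teachers are to be blinded. Parents are not stated to be, they take part in the intervention, and they supply two of the three measures. A positive parent report with a null teacher report is therefore plausible, and with three unranked primary measures it could be presented either way once the data are known.

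**Working it through.** **1. Reproduce the plan's figure.** Inputs from Sample size: difference 3, SD 6, two-sided alpha 0.05, power 0.80.

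n per arm = 2 × (1.960 + 0.842)² × 6² / 3² = 62.8, so 63. With 40% loss, 63 / 0.6 = 105 per arm and 210 in total. Both figures reproduce. Power at 63 per arm: the expected z is 0.5 × √(63/2) = 2.81, which gives 80.1%. All of this concerns one test of the parent SDQ.

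**2. Assumptions needed beyond the article.** It gives no correlations between measures and no effect size or SD for teacher SDQ or ECBI. I assume:
- correlation of parent with teacher report 0.3, and of parent SDQ with ECBI about 0.58 (0.55 to 0.6);
- correlation of T1 with T2 of 0.6 to 0.7;
- for joint power, 80% power on each measure.

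**3. Rule A: any positive measure counts.** With k independent tests at 0.05, familywise error = 1 − 0.95^k, which is 14.3% for k = 3 and 26.5% for k = 6. For correlated tests I simulated multivariate-normal z statistics and counted draws with any |z| > 1.96.

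| Reading | Tests | Familywise two-sided error |
|---|---|---|
| One mixed-model test for each of three measures | 3 | about 13% |
| Three measures, T1 and T2 tested separately | 6 | about 21-22% |

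Sensitivity: with equal correlations from 0.3 to 0.9 between all tests, the error runs from 13.6% down to 8.4% for three tests and from 24.1% down to 10.9% for six. It is above 5% throughout. These are two-sided rates; false claims of benefit alone are about half as frequent (about 11% for the six-test reading).

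**4. Rule B: all three must be positive.** Type I error is at most 5%. Joint power, with each measure at 80%:

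| Correlation between measures | Joint power |
|---|---|
| 0 (0.8³ = 0.512) | about 51% |
| 0.2 | about 55% |
| 0.5 | about 61% |
| 0.9 | about 72% |

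**5. What keeping three primary measures would take.** Bonferroni over three measures uses alpha = 0.05 / 3 = 0.0167, with critical value 2.394. Power per measure at 63 per arm = Φ(2.81 − 2.394), about 66%. To restore 80% per measure: n = 2 × (2.394 + 0.842)² × 4 = 83.8, so 84 evaluable per arm; 84 / 0.6 = 140 randomised per arm, 280 in total.

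**The case against.** The strongest reply is that the sample size section openly selects the parent SDQ for planning. Sizing a trial on one of several outcomes is common, and the stated alpha and power are correct for that measure. This stands, and the arithmetic is not in dispute. But the selection is expressly for sizing only. It does not remove primary status from the other two measures.

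A second reply is that the success rule, any alpha split and the primary time point are details that a journal article leaves to the full protocol or analysis plan. That also stands, and their absence is not the point here. The point is a mismatch between two statements the article does make: which measures are primary, and which one the error rate and power belong to.

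Some stronger readings are tempting, but the article does not support them:
- **Six to eight primary comparisons as a fact.** This counts T1 and T2 separately and, for eight, the ECBI as two scores. The planned mixed model can equally give one test per measure, hence three. Six to eight is an upper reading.
- **A conflict between the abstract and the outcome section.** The ECBI is completed by parents, so the abstract's reference to parents and teachers covers all three measures.
- **A stated error rate and power that apply to no primary measure.** They apply to the parent SDQ, which is one of the three.

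Finally, making the parent SDQ the sole primary outcome takes primary status from the only measure with a blinded informant and sits uneasily with the article's case for two informants. That is a real cost and is counted under the fix.

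**Conclusion.** The concern holds as a mismatch between the Outcome measures and Sample size sections. The stated 5% error and 80% power are right for the parent SDQ. They are not the operating characteristics of the three-measure primary outcome under either an any-positive or an all-positive rule.

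Under any-positive, error is roughly two and a half times nominal with three tests (13 / 5 = 2.6) and a little over four times with six (21 / 5 = 4.2). Under all-positive, joint power falls short of 80% by about 19 to 25 percentage points (80 − 61 and 80 − 55).

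The direction is firm: it holds at every correlation tried. The sizes rest on assumed correlations and, for joint power, on assumed 80% power for teacher SDQ and ECBI. The planned total need not change if the parent SDQ is made the sole primary outcome.

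**What to change.** In Outcome measures, name the parent-reported SDQ total problems score, which the sample size already powers, as the sole primary outcome. Attach one prespecified primary contrast: the SSTP-minus-CAU difference at one named time point, or one overall treatment effect from the mixed model. List teacher SDQ and ECBI as secondary, with the blinded teacher SDQ first as corroboration. The total stays at 210.

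Cost: a change of wording before the data are seen. Teacher SDQ and ECBI lose primary status, and the sole primary outcome is reported by parents who are not stated to be blinded, so the teacher result should be shown beside it.

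Alternative, if the sponsor wants all three to stay primary: state whether any or all must be positive, and restate the error rate or power accordingly. Under Bonferroni over three measures, that means either accepting about 66% power per measure with 63 evaluable per arm, or raising the total to 280 under the same 40% loss and an assumed effect size of 0.5 on each measure.

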### Other variables

In addition, data will be collected about the current use of health care and use of health care in the past (in the preceding four weeks, six months and longer than six months ago). Moreover, questions will be asked regarding the need for parental support and satisfaction with care.

Data on sociodemographic characteristics (parental education, family income, family structure, ethnicity, parental age and parental employment) and child medical conditions will be collected at baseline to adjust for potential differences between the intervention and control groups.

### Sample size

The parental SDQ score will serve as the primary outcome measure to determine the sample size. For a 3-point decrease in the SDQ total score, given a standard deviation (SD) of the SDQ of 6 points (an effect size of 0.5), at alpha = 0.05 (two-sided) and beta = 0.20, 63 children need to be included in each group (SSTP and CAU). With adjustment for a 'loss to follow-up' of about 40%, 210 children need to be included in the study, 105 children in each treatment condition.

Parents will be included if their child has an SDQ total problems score of 14 or higher. The prevalence rate of an SDQ ≥ 14 among children who are not under current treatment for their mental health problems is estimated at 55% [2]. Therefore, (2 × 105)/55% = 381 children with mild ID aged 5-12 years are required. Adjusting for 30% refusal to participate and 10% incomplete SDQs, 635 parents will have to fill in the SDQ.

### Randomisation procedure

After informed consent by the parents and application of the exclusion criteria by the researcher, the parents will be randomised to either SSTP or CAU. The randomisation will be based on a computer-generated randomisation algorithm. Individuals will be randomised per centre in each of the four participating centres in mixed blocks of four and six to prevent unequal randomisation within the centres [26]. If parents are randomised to SSTP, the intervention will start within four weeks of administering the screening questionnaire. Blinding will be imposed on the teachers, i.e. they will not know who is participating in which group. The SSTP trainers cannot be blinded to treatment status during the intervention, because blinding is apparently impossible.

### Statistical analyses

The results will be analysed on an intention to treat principle with all randomised participants, using all follow-up measures. Consequently, participants who filled out the questionnaire will be included in the analyses, regardless of whether or not they have completed the intervention.

The baseline characteristics of the parents in both research groups will be compared using Chi-squared tests for nominal and ordinal variables, and t-tests for continuous variables. The differences between the intervention and control condition over time will be assessed by mixed model techniques to consider factors that may influence the outcomes. If necessary, data on subjects lost to follow-up will be handled by extrapolation of the last observation or by sophisticated imputation techniques. Changes in the child's psychosocial problems and parenting characteristics will be expressed as standardised effect sizes with 95% confidence intervals. The CONSORT guidelines will be followed [14]. All the analyses will be carried out using SPSS 17.0.

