### Limitations

The study also has some potential limitations. Selective dropout may occur in the intervention group, i.e. a certain proportion of parents may not complete the study. Also, selective non-response may occur in the screening. People with lower incomes, more family problems and a lower IQ are at a higher risk of dropout or non-response. For example, parents with mild ID need a lot of practical support and research activities like filling out questionnaires may be difficult for them [29]. To prevent such selective non-response, we may assist parents in filling out the questionnaires.

Moreover, loss to follow-up may be high in this target population, potentially leading to biased results. To prevent this bias, all parents will receive assistance in filling out the questionnaire if they participate in the intervention study.

Another potential limitation is that we will not observe the parents' interaction with their child. Direct observation would provide the opportunity to precisely register the activities and behaviour of parents and their children during the intervention period. However, this method is costly and labour-intensive for both researchers and families [30]. Moreover, the observations themselves may affect the parent-child interactions, and may thus be a somewhat biased alternative as well.

Finally, in the study there is a short follow-up period of six months because studies about the effectiveness of parenting programmes establish findings at least on the short-term outcomes of family functioning, parenting skills and a child's psychosocial behaviour [31]. Nevertheless, this intervention aims to prevent developmental problems in children in the future, which leads to a limitation of this study being the short follow-up period. To determine long-term effects, there should be follow-up after a couple of years to assess the effects when the child is older [32].

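### The plan keeps last observation carried forward (LOCF) as an option with about 40% loss expected; for a child lost before T1 it would enter the selected screening score as the outcome

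*Protocol article*

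**What the plan says.** All of the following is in the Protocol article.

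- **Missing data (Statistical analyses).** "data on subjects lost to follow-up will be handled by extrapolation of the last observation or by sophisticated imputation techniques". The sentence is conditional, and it does not say which of the two routes applies or when. The same section plans mixed models for the comparison over time, and standardised effect sizes with 95% confidence intervals.
- **Visits (Trial design).** "There will be a screening before the intervention (T0), an assessment immediately after the intervention (T1) and a follow-up assessment after six months (T2". T0 is therefore the only measurement before T1.
- **Entry (Sample size).** "Parents will be included if their child has an SDQ total problems score of 14 or higher".
- **Outcome that sized the trial (Sample size).** "The parental SDQ score will serve as the primary outcome measure to determine the sample size".
- **Expected loss (Sample size).** "With adjustment for a 'loss to follow-up' of about 40%, 210 children need to be included in the study, 105 children in each treatment condition". The loss is not split by arm or by visit.
- **Dropout (Limitations).** "Selective dropout may occur in the intervention group". The section also says that loss may be high and may bias the results.

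**The concern.** The variable used to select children is also the baseline of the main outcome. A group chosen for high scores is expected to score lower on re-measurement even without treatment. A child who is measured again shows that fall and any treatment effect. A child who is lost before T1 and carried forward shows neither, because the change is zero by construction.

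Two things are at stake. First, the estimated effect shrinks in proportion to the early loss. Carried values are also counted as measurements, so the interval is too narrow and sits in the wrong place. Second, if the arms lose different shares, the missing fall no longer cancels between them, and a difference can appear where there is none. The mixed model already planned can use every observed score and does not need this step.

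**Working it through.** **1. The plan's own figures.** For 3 points, SD 6, two-sided alpha 0.05 and power 0.80: n = 2 × (1.96 + 0.84)² × 6² / 3² = 62.7, so 63 per group. Inflated for loss, 63 / (1 − 0.40) = 105 per group, 210 in total. All three stated figures reproduce. At 40% loss, 42 of 105 children per arm lack a final score.

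**2. Size of the selection.** Inputs from the Sample size section are SD 6 and 55% of screened children at or above 14. Normality is assumed.
- Unselected mean: 14 + 6 × 0.126 = 14.75.
- Mean of those at or above 14: 14.75 + 6 × 0.396 / 0.55 = 19.07.
- Expected fall on re-measurement: m = (1 − r) × (19.07 − 14.75) = (1 − r) × 4.32. This is 1.73 points at r = 0.6 and 1.30 at r = 0.7 (0.86 to 2.16 for r = 0.8 to 0.5). The correlation r is assumed.

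**3. What LOCF estimates.** Let dT and dC be the shares lost before T1 on SSTP and CAU, with dropout unrelated to outcome and equal T1 and T2 means. Then

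LOCF effect = (1 − dT)(m + 3) − (1 − dC)m.

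With equal loss, m cancels:
- All 40% lost before T1: 0.60 × 3 = 1.8 points.
- Half of it (20%) lost before T1: 0.80 × 3 = 2.4 points.

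With 50% loss on SSTP and 30% on CAU (illustrative only; the documents give no split):
- All before T1: 0.50 × 4.30 − 0.70 × 1.30 = 1.24 at r = 0.7, and 0.50 × 4.73 − 0.70 × 1.73 = 1.15 at r = 0.6.
- Half before T1: 0.75 × 4.30 − 0.85 × 1.30 = 2.12, and 0.75 × 4.73 − 0.85 × 1.73 = 2.08.
- No true effect: (dC − dT) × m = −0.20 × 1.30 = −0.26 to −0.20 × 1.73 = −0.35 if all precede T1, and −0.13 to −0.17 if half do. The minus sign means against SSTP.

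If CAU lost more, the spurious difference would favour SSTP. Any further improvement shared by both arms would add to m and enlarge it.

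**4. Simulation.** 105 per arm, T0 truncated at 14, random dropout, regression on arm and T0, 4,000 trials per scenario, r = 0.6 and 0.7. For the half-early rows the T1–T2 correlation was set at 0.7.

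| Loss SSTP/CAU | Lost before T1 | LOCF estimate (truth 3.0) | 95% CI coverage | Rejection, true effect 3 | Rejection, no effect |
|---|---|---|---|---|---|
| 40/40 | all | 1.8 | 35–46% | 88–94% | 5% |
| 40/40 | half | 2.4 | 82–85% | 97–99% | 5% |
| 50/30 | all | 1.2 | 8–12% | 51–66% | 9–10% |
| 50/30 | half | 2.1 | 65–70% | 91–96% | 6% |

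The same regression on observed scores only gave about 3.0 points, about 95% coverage and about 5% rejection under no effect in every row.

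**5. Interval width.** At r = 0.7 the residual SD is 6 × √(1 − 0.49) = 4.28. With 63 observed per arm the standard error is about 4.28 × √(2/63) = 0.76. With LOCF and all losses early, the estimate's standard deviation across simulated trials was 0.52. The interval is narrower because 84 carried scores count as data. The low coverage comes from this narrow interval lying around 1.8 instead of 3.0.

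**The case against.** The strongest defence is that LOCF is conditional, is one of two alternatives and stands beside a mixed model. An article may also leave the choice between fallback methods to an analysis plan that is not shown. This stands as far as it goes: a reader might infer that the trial will use LOCF, and the text does not say so. What can fairly be criticised is that the article names LOCF as acceptable.

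Other stronger readings also fail:

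- **That 1.8 points is the expected result.** It needs every loss to fall before T1. A family lost between T1 and T2 would carry its T1 score.
- **That the plan forecasts unequal dropout.** The Limitations section says selective dropout may occur, and gives no size. The Participants section plans visits to all families for the second and third questionnaires, and the Limitations section promises help with completing them. The 50/30 split is only an illustration.
- **That LOCF would produce false claims of benefit.** With equal loss, type I error stays near 5%. With heavier loss on SSTP, the spurious difference goes against SSTP. Power also holds up at 40/40; the estimate and interval are what suffer.
- **That the section contradicts itself on who is analysed.** It promises all randomised participants and then says "Consequently, participants who filled out the questionnaire will be included in the analyses". Every family completes the screening questionnaire before randomisation, so all have T0 data. The sentence goes on to say that completing the intervention is not required, which is ordinary intention-to-treat wording.

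Two limits of the check also stand. Dropout was simulated as random, so the observed-data analysis is unbiased by construction; if loss depends on unseen scores, the mixed model can be biased too. The check also used a single-follow-up regression, not the mixed model itself. Finally, selection acts directly only on the parent SDQ. For the teacher SDQ and the ECBI, LOCF would carry a pre-treatment value that was not itself the entry criterion.

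**Conclusion.** The point holds as a fault in what the plan permits. With about 40% loss expected, LOCF should not remain available for an outcome whose baseline was selected at 14 or higher.

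At equal 40% loss, the 3-point design effect would be estimated as 1.8 points if all losses precede T1 and 2.4 if half do, a loss of 40% or 20% of the effect. Coverage would be about 35–46% and 80–85%. With the illustrative 50/30 loss the estimate would be about 1.2 to 2.1 points. Under no effect there would then be a spurious difference of about 0.1 to 0.35 points against SSTP, with rejection of about 5–10%.

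The 3 points, SD 6, 55%, 40% and 105 per arm are the plan's. Normality, the correlations, random dropout, equal T1 and T2 means, the timing of loss and any split by arm are assumptions.

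**What to change.** Delete the LOCF option from the Statistical analyses section. State that the primary analysis is the likelihood-based mixed model with all randomised families and all observed T0, T1 and T2 scores, without single imputation. If imputation is needed, specify multiple imputation with T0 and arm in the imputation model, in place of the open reference to imputation techniques.

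A sensitivity analysis for data missing not at random would be a useful addition given the stated worry about selective dropout, but it is optional.

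The cost is the wording of one or two sentences. No new data are needed, and 63, 105 and 210 stay as they are.
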